### Sample Size and Power Calculation

The sample size calculation is based on a random intercept model comparing the primary outcome (PHQ-ADS at T3) between treatment conditions while accounting for the nested structure of the data. Although this model is simpler than the target statistical analyses for the primary outcome presented below, it allows to avoid speculative assumptions about numerous unknown model parameters. The focal hypothesis is that both intervention groups PSYCHOnlineTHERAPY_fix/flex_ are not inferior to CBT_standard_ (= non-inferiority trial). Non-inferiority is assumed if the confidence interval (CI) of the standardized mean comparissson between PSYCHOnlineTHERAPY_fix/flex_ is completely above SMD = −0.24, which is considered as a lower threshold of clinical significance (49). We assume one-sided tests with α = 0.025 (Bonferroni-adjusted) and 1-ß = 0.8, an intra-cluster correlation coefficient (ICC) of 0.01 with a median cluster size of 12 eligible patients as feasible number to be recruited within the recruitment period. Based on these assumptions, the present trial aims at a sample size of 25 psychotherapy outpatient practice clusters and *n* = 300 patients per study arm with an allocation ratio of 1:1:1 (PSYCHOnlineTHERAPY_fix_, PSYCHOnlineTHERAPY_flex_, CBT_standard_; for formulas see (50).

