### Statistical Analyses

#### Clinical Analyses

The primary outcome will be analyzed using a three-level random slope model with measurement points nested in patients and patients nested in therapists. We will include data on depression and anxiety severity assessed at four measurement points, including baseline (T0), inter-session assessments at six (T1) and 12 weeks (T2) follow-up, and post-treatment at 18 weeks post-inclusion (T3). Depression and anxiety severity will be predicted from log-transformed time (i.e., weeks since baseline), dummy-coded treatment groups, and their interactions. Random intercepts and slopes will be included to account for unexplained heterogeneity in baseline status and rate of change, both at the level of patients and therapists. The focal tests of non-inferiority will be based on the bootstrap CIs of the interactions between time and groups. All statistical analyses will be performed based on intention-to-treat (ITT) principle. Patterns of missing data will be examined and analyses will be corrected for missing data by applying multiple imputation. Additional multiple PP analyses will be conducted including only patients that provided data.

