#### Mobile Sensing

The analysis of the mobile sensing data will be divided into two parts. Firstly, correlation analyses will be conducted to investigate associations between digital features (e.g., smartphone usage time) and mental health outcomes. Correlation coefficient r will be used for the analysis, which ranges between 0 (no relationship) to 1 (perfect relationship; −1 perfect negative relationship). For all correlation analyses, the alpha-level will be 5%. *P*-values will be adjusted for multiple testing using the procedure proposed by Holm (107, 108). Full information maximum likelihood will be applied to deal with missing values in the correlation analysis (108, 109). Secondly, we will build different prediction models to predict mental health. Both “traditional” multilevel models relying on significance tests and machine learning will be used. Building and modifying machine learning models is a highly iterative process with many changing factors to find the optimal model (e.g., architecture, optimizer, included features). Hence, defining a-priori model is impossible. However, a range of approaches will be tested, this includes: Random Forest models, Support Vector Machine (SVM), XGBoost (XGB), K-Nearest Neighbor (KNN), and Logistic Regression [LR; (110–114)].

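### The planned 80% power holds for each blended arm separately, not for both arms as the focal hypothesis reads; Holm in place of Bonferroni would raise power at the same familywise error with no extra patients

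*Protocol article*

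**What the plan says.** All the relevant choices stand in the Protocol article, Methods, Sample Size and Power Calculation.

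- **Hypothesis:** "The focal hypothesis is that both intervention groups PSYCHOnlineTHERAPY_fix/flex_ are not inferior to CBT_standard".
- **Decision rule:** non-inferiority is concluded if the confidence interval for the standardised mean difference "is completely above SMD = −0.24, which is considered as a lower threshold of clinical significance".
- **Error rates:** "We assume one-sided tests with α = 0.025 (Bonferroni-adjusted) and 1-ß = 0.8".
- **Clustering:** "an intra-cluster correlation coefficient (ICC) of 0.01" and "with a median cluster size of 12 eligible patients".
- **Result:** 25 practice clusters and 300 patients per arm, allocated 1:1:1. The section does not say whether the 80% refers to one comparison or to both.

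The same section says that sizing uses a simpler model than the planned primary analysis. Under Statistical Analyses, Clinical Analyses, that analysis is a three-level model over T0 to T3, with the non-inferiority tests based on bootstrap confidence intervals; "analyses will be corrected for missing data by applying multiple imputation". Nothing there changes the multiplicity rule. Elsewhere, for the smartphone correlations (Statistical Analyses, Mobile Sensing), p-values are "adjusted for multiple testing using the procedure proposed by Holm".

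**The concern.** The 80% stands beside a hypothesis about both arms, so a reader can take it as the power to show that both are non-inferior. If it belongs to a single comparison, the power for both is lower, because two correlated tests must succeed together.

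The adjustment is a second, linked matter. Splitting alpha by Bonferroni protects separate claims for each arm, but Holm gives the same protection and rejects at least as often. If the plan keeps Bonferroni, it gives up power on its primary question that it could have without recruiting anyone more.

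**Working it through.** **Inputs, all from the Sample Size section:** margin 0.24 on the SMD scale (SD 1), one-sided alpha 0.025 per comparison, power 0.80, ICC 0.01, cluster size 12, 300 per arm, 1:1:1.

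**Assumptions added here:** a true difference of 0 in both arms (not stated, but it reproduces the plan's figure), a normal approximation, and complete T3 data unless noted.

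**1. Reproduce the plan's figure.**
- Design effect = 1 + (12 − 1) × 0.01 = 1.11.
- n per arm = 2(1.960 + 0.842)² / 0.24² × 1.11 = 272.5 × 1.11 = 302.5. The plan has 300.
- Other per-test alphas do not give 300: 0.0125 needs about 367 and 0.05 about 239.

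So the 80% belongs to one comparison at one-sided 0.025.

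**2. Power per comparison at 300.**
- SE = √(2 × 1.11 / 300) = 0.0860.
- Expected z = 0.24 / 0.0860 = 2.790.
- Power = Φ(2.790 − 1.960) = 0.797.

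**3. Power for both arms, Bonferroni.** Equal arms sharing one control give a correlation of 0.5 between the two test statistics. With Z₁ and Z₂ bivariate normal, each with mean 2.790:
- P(Z₁ > 1.960 and Z₂ > 1.960) = 0.683.
- At least one arm: 2 × 0.797 − 0.683 = 0.911.

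**4. Power with Holm.** The stronger arm is tested at one-sided 0.025 (critical value 1.960). If it passes, the other is tested at 0.05 (critical value 1.645).
- P(Z₁ > 1.960 and Z₂ > 1.645) = 0.733.
- Both arms: 2 × 0.733 − 0.683 = 0.783.
- A given arm: 0.797 + (0.733 − 0.683) = 0.847.
- At least one arm: 0.911, as before, because the first step is the same.

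| Complete T3 data, 300 per arm | Bonferroni | Holm |
|---|---|---|
| A given arm | 0.797 | 0.847 |
| Both arms | 0.683 | 0.783 |
| At least one arm | 0.911 | 0.911 |
| n per arm for 80% on both | about 377 | about 311 |

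A check by 2 million simulated draws, with per-comparison power set at exactly 0.80, gave 0.688 (Bonferroni) and 0.787 (Holm) for both arms. The formulas give 0.687 and 0.787 for that case.

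**5. Missing T3 data.** The sizing section shows no allowance for it, and the article gives no expected rate. The rates below are assumptions. Missingness reduces both n and cluster size: at 20%, n = 240, cluster size = 9.6, design effect = 1.086, SE = 0.0951, z = 2.523.

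| Assumed missing at T3 | Per comparison (0.025) | Both, Bonferroni | Both, Holm |
|---|---|---|---|
| 10% | 0.758 | 0.631 | 0.740 |
| 20% | 0.713 | 0.573 | 0.688 |
| 30% | 0.660 | 0.509 | 0.628 |

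**6. What baseline information could recover.** As an illustration only, let the variance shrink by 1 − r², with r an assumed baseline-to-T3 correlation that the article does not give. Power for both arms under Bonferroni is then 0.73 at r = 0.3 with complete data. At r = 0.5 it is 0.83 with complete data, 0.78 with 10% missing and 0.73 with 20% missing.

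**The case against.** The strongest reply is that an alpha split makes sense only if each arm can be claimed on its own. On that reading the sentence about both groups states two parallel hypotheses, and 80% per comparison is the right figure. If success required both arms, no split would be needed, and testing each at one-sided 0.05 would give 0.793 for both. This largely stands: Bonferroni is valid and the 80% is not a miscalculation. What remains is that the text does not say which reading applies, and that Holm does better than Bonferroni for per-arm claims too.

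Second, the decision rule rests on confidence intervals, and Bonferroni gives one level for both arms. Holm judges the second arm on a 90% interval, and simultaneous intervals become less simple. That is a real cost, though a small one. The use of Holm for the sensing correlations is only a weak precedent, since it concerns p-values in an optional sub-study.

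A reader might infer two stronger conclusions:
- **That the trial as planned has nearly a one-in-three chance of missing its focal hypothesis when both arms truly equal CBT.** The documents do not support this. The 0.683 is for the simplified T3 comparison, and the planned longitudinal model may do better by an amount that the article does not quantify. The attrition rates above are likewise assumed.
- **That Bonferroni gives away ten points of power in general.** It does so only for success in both arms. The difference is five points for a given arm and nil for at least one.

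**Conclusion.** The point holds as a matter of clarity and efficiency, not as an error that invalidates the design. At 300 per arm the stated 80% is power per comparison. Under the plan's own sizing assumptions, with complete data and a true difference of zero, power for both arms is about 68% with Bonferroni. Holm would bring that to about 78%, and power for a given arm from about 80% to about 85%.

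The one-sided 5% familywise level is inferred from the Bonferroni-adjusted 0.025, and the joint figures use the 0.5 correlation that follows from equal arms with a shared control. Power under the planned longitudinal model with realistic missing data cannot be determined from the article in either direction.

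**What to change.** Before any unblinded analysis:

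1. Replace Bonferroni with Holm for the two primary comparisons. Test the arm with the stronger evidence at one-sided 0.025 (95% CI above −0.24). If it passes, test the other at one-sided 0.05 (90% CI above −0.24). State both levels in advance.
2. State that non-inferiority is claimed for each arm separately.
3. Restate the power in the Sample Size section as about 80% per comparison with complete T3 data, and about 68% (Bonferroni) or 78% (Holm) for both arms.
4. Add the same figures under the T3 missingness that the investigators expect, noting that the longitudinal model may recover part of the loss.

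This costs wording and restated figures, and no extra patients. If a single confidence level for both arms is valued more than the power, Bonferroni can stay, but items 2 to 4 are still needed.

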### Assessments

All assessments will be conducted online (patient and therapist self-reports) or telephone-based (standardized clinical interview SCID-5, HAM-A, QIDS-C). For an overview of instruments at baseline (T0), inter-session assessments at six (T1) and 12 weeks (T2) follow-up, as well as 18 weeks (T3; assumed as post-treatment), 24 weeks (T4) and 12 months post-inclusion follow-up (T5) see Tables 3, 4. PSYCHOnlineTHERAPY might be continued with further follow-up assessments (2–5-year follow-up assessments) in case of patients' informed consent and given follow-up assessment resources.

**Table 3 T3:** Overview of the assessments (patients).

**Variable**	**Instrument**	**Time of measurement**					
		**T0**	**T1**	**T2**	**T3**	**T4**	**T5**
**Online-questionnaires (self-rated)**							
Depression and anxiety	PHQ-ADS	X	X	X	X	X	X
Quality of Life	AQOL	X			X	X	
Patient satisfaction	ZUF-8				X		
Working alliance	WAI-SR		X		X		
Cost-effectiveness	TIC-P	X			X	X	
Sociodemographics	SR	X	X				
Risk factors	SR	X					
Medication	SR	X			X	X	X
Reasons for dropout	SR				X		
Childhood trauma	CTS	X					
Social support	F-SozU K-6	X			X		
Negative effects	NEQ				X		
Suicidal and self- injurious thoughts and behaviors	C-SSRS	X			X		
Personality functioning	LPFS-BF 2.0	X					
Self-care	SR	X	X	X	X		
Self-management	SMST	X	X	X	X		
Self-efficacy	MHSES	X	X	X	X		
Therapeutic agency	TAI		X	X	X		
Empowerment	SR				X		
CBT-Skills	CBTSQ	X	X	X	X		
Homework implementation	SR		X	X	X		
Loneliness	UCLA	X			X		
Expectations/Credibility	CEQ	X			X		
Attitudes toward blended therapy	APOI	X			X		
Individual therapy goals	FRAPT	X			X		
**Interviews (clinician-rated)**							
Comorbid disorders, severity, chronicity; remission	SCID-5	X			X		
Depression response	QIDS	X			X		
Anxiety response	HAM-A	X			X		
Serious adverse events	Checklist				X		

*T0, Baseline; T1, 6 weeks; T2, 12 weeks; T3, 18 weeks post inclusion; T4, 24 weeks post inclusion; T5, 12 months post inclusion follow-up; PHQ-ADS, Patient Health Questionnaire Anxiety and Depression Scale; AQOL, Assessment of Quality of Life; ZUF-8, Questionnaire for Patient Satisfaction-8; WAI-SR, Working Alliance Inventory—Short Revised; TIC-P, Trimbos Institute and Institute of Medical Technology Questionnaire for Costs Associated with Psychiatric Illness; SR, Self-Report Assessment; CTS, Childhood Trauma Screener; F-SozU K-6, Perceived Social Support Questionnaire brief form; NEQ, Negative Effects Questionnaire; C-SSRS, Columbia-Suicide Severity Rating Scale; LPFS-BF 2.0, Level of Personality Functioning Scale Brief Form 2.0; SMST, Self-Management Self-Test; MHSES, Mental Health Self Efficacy Scale; TAI, Therapeutic Agency Inventory; CBTSQ, Cognitive-Behavioral Therapy Skills Questionnaire; UCLA, UCLA Three-Item Loneliness Scale; CEQ, Credibility-Expectancy-Questionnaire; APOI, Attitudes toward Psychological Online Interventions; FRAPT, Fragebogen zur Messung persönlicher Therapieziele [Questionnaire for measuring personal therapy goals]; SCID-5, Structured Clinical Interview for DSM-5; QIDS, Quick Inventory of depressive Symptomatology; HAM-A, Hamilton Anxiety Rating Scale*.

**Table 4 T4:** Overview of the assessments (therapists).

**Variable**	**Instrument**	**Time of measurement**					
		**T0**	**T1**	**T2**	**T3**	**T4**	**T5**
Working alliance	WAI-SR-T				X		
Sociodemographics	SR	X					
Attitudes toward blended therapy	APOI	X			X^*^		
Attitudes toward evidence-based practice	EBPAS-D36	X					
Willingness to use digital health interventions	SR	X					
Barriers/facilitators in the use of digital health interventions	SR	X					
Acceptance of components of blended therapy	SR	X					
Determinants of behavioral change	TDF				X^*^		
Degree of normalization	NoMAD				X^*^		

*T0, Baseline; T1, 6 weeks; T2, 12 weeks; T3, 18 weeks post inclusion; T4, 24 weeks post inclusion; T5, 12 months post inclusion follow-up; WAI-SR-T, Working Alliance Inventory—Short Revised therapist version; SR, Self-Report Assessment; APOI, Attitudes toward Psychological Online Interventions; EBPAS-D36, Evidence-based Practice Attitude Scale-36; TDF, Theoretical Domain Framework Questionnaire; NoMAD, Normalization Measure Development Questionnaire;*

* *Assessment at the end of the entire study*.

#### Primary Outcome

The primary outcome is depression and anxiety severity at post-treatment 18 weeks post-inclusion (T3), assessed with the Patient Health Questionnaire Anxiety and Depression Scale [PHQ-ADS; 16 items, score range: 0–48; (51)]. Depression and anxiety symptoms at all other assessments will be considered as secondary outcomes. PHQ-ADS is the combined sum score of the questionnaires Generalized Anxiety Disorder Screener (GAD-7) and Patient Health Questionnaire (PHQ-9) as a composite measure of depression and anxiety, with good internal consistency [α = 0.88–0.92; (51)].

#### Secondary Outcomes

Depression and anxiety remission will be assessed with the Structured Clinical Interview [SCID-5; (52)] as a comprehensive, structured interview designed to be used by trained interviewers for the assessment of mental disorders according to the definitions and criteria of DSM-5. It enables a reliable, valid, and efficient assessment of depressive disorders (52). The SCID-5 will also be used in order to obtain additional information about comorbid disorders, severity of disorders, and chronicity.

Depression response will be assessed with the Quick Inventory of Depressive Symptomatology in its clinician-rated version [QIDS-C; 16 items, score range: 0–27; (53)]. It encompasses the criteria sleep, depressed mood, appetite/weight change, concentration/decision making, self-outlook, suicidal ideation, loss of interest or pleasure, energy/fatigability, and psychomotor changes. QIDS depressive symptom scores are used to determine depression response in accordance to the recommendations of Jacobson and Truax (54). Trained interviewers will conduct the clinician-rated version QIDS-C for which good psychometric properties and internal consistencies between α = 0.81 and α = 0.95 are reported (55).

Anxiety response will be assessed with the Hamilton Anxiety Rating Scale [HAM-A; 14 items, score range: 0–56; (56, 57)] which measures psychic and somatic symptoms of anxiety. Like the QIDS-C and the SCID-5, the HAM-A is clinician-rated and therefore will be conducted by a trained interviewer. It is characterized by a high inter-rater reliability and internal consistency (α = 0.85; 57). HAM-A anxiety symptom scores are used to determine anxiety response in accordance to the recommendations of Jacobson and Truax (54).

Health-related quality of life will be assessed with the self-report questionnaire Assessment of Quality of Life [AQoL-8D; 35 items; (58, 59)] including the unweighted responses subscales physical super-dimension (range: 10–51) and psychosocial/mental super-dimension (range: 25–125) and a total score (range: 35–176). The AQoL-8D is characterized by a high Cronbach's Alpha of 0.96 and good psychometric properties (58).

Patient satisfaction will be assessed with a German short version [ZUF-8; eight items, score range: 8–32; (60)] of the Client Satisfaction Questionnaire [CSQ; (61)]. Higher scores are indicative for higher satisfaction. Internal consistency of the ZUF-8 is reported with a Cronbach's Alpha of 0.90 (60). In addition, reasons for dissatisfaction with the intervention will be assessed with 9 self-developed items.

Working alliance will be assessed with the German version (62) of the Working Alliance Inventory [WAI-SR; 12 items, score range: 12–60; (63)]. It covers the three subscales (a) agreement on tasks (four items), (b) agreement on goals (four items), and (c) development of an affective bond (four items). For the German Version, internal consistencies between α = 0.81 and α = 0.91 were reported for the subscales and internal consistencies between α = 0.90 and α = 0.93 for the total score (62, 64). Participants will complete the WAI-SR at T1 and at T3. Therapists only at T3. This will allow for a comparison between patients' and therapists' view on working alliance.

Psychotherapy adherence will be assessed by means of the number of completed online- and standard sessions. Per-protocol (PP) adherence is operationalized by the percentage of participants that completed their psychotherapy as recommended by their therapist (therapist-rating). Reasons for dropout are assessed by six items at post-treatment (T3; patient-rating).

#### Covariates

As potential moderating variables, demographic (e.g., gender, age, education) and medical information (e.g., previous treatment, medication) will be recorded at baseline. Further, a variety of potential predictors will be included to assess moderators and mediators of psychotherapy effects.

The following information of therapists will be assessed with six items: age, gender, time since licensed as therapist, number of inhabitants at the location of the practice, and experience with digitally supported psychotherapy. Patient characteristics will be assessed with 15 self-report items including information on age, gender, body height, weight, education, employment, income, relationship status, children living in the household, ethnicity, migration, previous treatment, number of inhabitants of the place of residence, and distance to the practice of the therapist.

Further patient characteristics (risk factors) that potentially predict depression and anxiety symptoms will be assessed by means of 27 self-report items. The following factors will be assessed: smoking, drug use, alcohol consumption, diet quality, social status, minority, discrimination, self-perceived energy, family history of mental illness, adverse childhood experiences (parental death or divorce), accidents, physical and sexual abuse, and physical activity.

Existing medication at the beginning of the study will be assessed at baseline (three items). Potential initiation of new medication will be assessed at post-treatment (two items) and at follow-ups (three items).

Childhood trauma will be assessed with the Childhood Trauma Screener [CTS; five items, score range: 5–25; (65, 66)]. Its internal consistency is reported to be α = 0.76 (65).

Social support will be assessed with the brief form of the Perceived Social Support Questionnaire [F-SozU K-6; six items, score range: 6–30; (67)]. Higher scores indicate higher perceived social support. The measure is characterized by a high Cronbach's alpha of 0.90 (67).

Personality functioning will be assessed with the German version of the Level of Personality Functioning Scale—Brief Form 2.0 [LPFS-BF 2.0; 12 items, score range: 12–48; (68)]. Personality functioning is divided into the two subscales interpersonal-functioning (six items) and self-functioning (six items). The internal consistency of the total scale is reported to be α = 0.82 (69).

Self-management will be assessed with the Self-Management Self-Test (SMST; five items, score range: 0–20; 70). Higher scores are indicative for better self-management competence. The SMST has been shown to have good psychometric properties with a Cronbach's Alpha of 0.80 (70).

Self-efficacy will be assessed with the Mental Health Self Efficacy Scale [MHSES; six items, score range: 6–60; (71)]. The instrument shows a Cronbach's Alpha of 0.89 (71).

Self-care will be assessed by means of four items (score range: 0–34) that were newly developed for this study. They consist of statements about having and taking time, personal resources for oneself, and the engagement with therapy contents at home.

Therapeutic agency will be assessed with two selected subscales of the Therapeutic Agency Inventory [TAI; 10 items; (72)]. The dimensions therapy-related processing (five items, score range: 1–5) and therapist-oriented passivity (five items, score range: 1–5) will be used within our study. Higher scores indicate higher levels of therapeutic agency. Internal consistency of the subscales is reported with α = 0.79 (therapy-related processing) and α = 0.73 [therapist-oriented passivity; (72)].

Empowerment will be assessed with two open-ended questions. Patients will be asked whether and how the intervention contributed to a feeling of strength and confidence and how they experience this in their everyday life.

CBT-skills will be assessed with the Cognitive-Behavioral Skills Questionnaire [CBTSQ; 16 items; (73)]. The measure comprises the two subscales behavioral activation (seven items, score range: 1–5) and cognitive restructuring (nine items, score range: 1–5). Higher scores are indicative of greater use of CBT-skills. Internal consistency is reported to be α = 0.88 (cognitive restructuring) and α = 0.85 [behavioral activation; (73)].

Homework implementation will be assessed with three self-developed items regarding adherence to exercises between the sessions, levels of difficulty in homework completion, and reasons for non-adherence.

Loneliness will be assessed with the UCLA Three-Item Loneliness Scale [UCLA; three items, score range: 3–9; (74)]. Higher scores are indicative for greater loneliness. It is characterized by a Cronbach's Alpha of 0.72 (74).

Expectations and credibility regarding the intervention will be assessed with the Credibility/Expectancy Questionnaire [CEQ; six items; (75, 76)]. The CEQ consists of the two distinct factors credibility (three items, score range: 3–27) and expectancy (three items, score range: 3–27). In order to re-evaluate expectancies of patients, treatment credibility will be assessed again at post-treatment (T3). Cronbach's Alpha of the total scale is ranging between α = 0.84 and α = 0.85, between α = 0.79 and α = 0.90 for the expectancy factor, and between α = 0.81 and α = 0.86 for the credibility factor (76).

Attitudes toward blended therapy will be assessed with selected subscales of the Attitudes toward Psychological Online Interventions Questionnaire [APOI; four items patients/12 items therapists; (77)] which was adapted to blended therapy for this study. For patients the subscale confidence in effectiveness (four items, score range: 1–5) will be used. From the therapist version we will use the following three subscales: skepticism and perception of risk (four items, score range: 1–5), confidence in effectiveness (four items, score range: 1–5), and technologization threat (four items, score-range: 1–5). Depending on the specific subscale higher scores indicate a more negative or positive attitude toward blended therapy. Internal consistency of the total scale is reported to be α = 0.77 with the subscales ranging from α = 0.62–α = 0.72 (77).

Individual therapy goals will be assessed with 4 selected subscales of the “Fragebogen zur Messung persönlicher Therapieziele” [Questionnaire for measuring personal therapy goals] [FRAPT; 31 items; (78)]. The subscales cover the overall goal categories trust in yourself and others (14 items, score range: 0–3), active confrontation with oneself and the disease (nine items, score range: 0–3), coping with depression and anxiety (four items, score range: 0–3), and family and improvements in the family and socioeconomic conditions (four items, score range: 0–3). Internal consistencies of the subscales are ranging from α = 0.67–α = 0.92 (78). Individual therapy goals will be assessed at T0 and their achievement will be evaluated with an adapted version of the measure at T3.

Attitudes toward evidence-based practice will be assessed with selected subscales of the German version of the Evidence-based Practice Attitude Scale-36 [EBPAS-D36; 12 items; (79)]. We will use the scales openness (three items, score range: 0–4), divergence (three items, score range: 0–4), limitations (three items, score range: 0–4), and balance (three items, score range: 0–4). For the English version Cronbach's Alpha is reported to range between α = 0.60 and α = 0.90 for the used subscales (80).

Three newly developed scales will be employed to assess therapists' willingness to use digital health interventions (six items, score range: 0–4), their experiencing of barriers and facilitators in the use of digital health interventions (eight items, score range: 0–4), and their acceptance of components of blended therapy (nine items, score range: 0–4).

Determinants of behavioral change that influence the behavior in health care settings when new interventions are implemented will be assessed with a theoretical domains framework (TDF) questionnaire [32 items; (81)] including the following dimensions: knowledge (four items, score range: 1–7), skills (three items, score range: 1–7), social/professional role and identity (four items, score range: 1–7), beliefs about capabilities (three items, score range: 1–7), optimism (two items, score range: 1–7), beliefs about consequences (two items, score range: 1–7), intentions (four items, score range: 1–7/1–10), memory, attention, and decision processes (four items, score range: 1–7), environmental context and resources (two items, score range: 1–7), social influences (two items, score range: 1–7), and emotion (four items, score range: 1–7).

The Normalization Measure Development Questionnaire [NoMAD; 20 items, score range: 0–80; (82)] assesses the extent to which the newly implemented intervention PSYCHOnlineTHERAPY is a normal part of the daily working routine of therapists. The measure is characterized by a Cronbach's Alpha of 0.89 (83).

Documentation of the therapy process will be performed by participating therapists for each of their patients via tablet at the beginning and at the end of the therapy process and after each session regarding homework assignments, topic of the session, therapeutic techniques, serious adverse events, and orientation toward individual therapy goals.

